#### Patients

We will extract electronic health record (EHR) data for eligible patients with a baseline diagnosis of hypertension, empanelment (assignment) to primary care providers in participating clinics, and at least one visit and one recorded blood pressure measurement within the past 12 months, consistent with National Committee for Quality Assurance (NCQA) Healthcare Effectiveness Data and Information Set (HEDIS) specifications [39]. We will extract EHR data at baseline and after Years 1, 2, and 3. We will not contact, consent, or incentivize patients.

### Implementation strategies

We will use patient- and provider-focused strategies to facilitate use of tailored EBPs to improve the management of hypertension in primary care. The tailored EBPs are based on the Kaiser Bundle [11] and additional practices relevant to our study context. Table 3 describes the EBPs, their adaptations for the study, and the patient- and provider-focused strategies aimed at encouraging EBP uptake.

**Table 3 Tab3:** Provider- and Patient-focused Implementation Strategies for Evidence-based practices

Evidence-based practice	Adaptations	Usual Strategies	Provider-Focused Strategies	Patient-Focused Strategies
1. **Hypertension Registry (Kaiser Bundle)** Clinics use the HTN registry to identify patients with inadequately controlled BP or no PCP appointment in the last 3 months, send reminders to the patient to schedule a PCP appointment, and notify care teams	Not Applicable	A HTN registry is not used routinely for patient or provider communication	Study team provides Clinic Champions with a list of patients with uncontrolled HTN who have had no PCP appointment in the last 3 months and no PCP appointment scheduled in the next 3 months	Study team identifies patients in the HTN registry with uncontrolled BP, no PCP appointment in the last 3 months, and no PCP appointment scheduled in the next 3 months, and sends reminders to the patient to schedule a PCP appointment Patients on the HTN registry may receive a link to culturally- and linguistically-tailored HTN educational materials via text message or the patient portal
2. **Home Blood Pressure Monitoring** Clinics utilize a standardized workflow to provide home BP monitors to all patients with HTN	This EBP was included to reflect updated guidelines on home BP monitoring, staff input, and changes in health plan policies	Not all providers are familiar with the workflow for ordering home BP monitors through insurance for eligible patients. Logistical barriers, such as backordered monitors, have been reported. For patients without insurance, free home BP monitors are provided through a patchwork of funding sources	Provider webinars (PCP, CHW, Nurse) describe standardized workflows for providing BP monitors to eligible patients through prescription or referral to the health plan and for reviewing and documenting home BP readings through the patient portal	Patient educational materials encourage patients to obtain a home BP monitor and how to ask a provider about ordering one. Once they have a monitor, patient is taught how to measure and log their BP, either in the patient portal or on a paper log they bring to clinic
3. **Standardized Blood Pressure Measurement (Kaiser Bundle)** Clinics use a standardized protocol for taking BP and have trained clinicians on this protocol	This EBP was adapted to incorporate standardized measurements at home, reflecting updated home BP monitoring guidelines	No specific implementation process exists for standardizing BP measurement across clinics and providers	Provider webinars describe how to use standardized BP measurement. Illustrated posters outlining standardized BP measurement practices are posted in clinic rooms where vitals are taken	Patients who receive home BP monitors receive training on standardized BP measurement practices Patient educational materials describe how to measure BP at home
4. **Treatment Intensification Protocol with Fixed Dose Combination Medications (Kaiser Bundle)** Patients with high BP are treated using fixed-dose combination pills, which can improve medication use, adherence, and BP control	This was adapted to reflect LAC DHS updated formulary. Based on clinician input, we developed provider webinar on fixed-dose combination medications	LAC DHS developed an HTN Expected Practices guide based on national guidelines, but uptake varies by clinic. Providers described challenges in interpreting multiple national guidelines. Intensification protocols and fixed-dose combination medications are not specifically emphasized in the Expected Practices	Provider webinars increase awareness of the efficacy and availability of combination medications in the formulary and LAC DHS HTN Expected Practices	Patient education materials describe HTN medications, including fixed-dose combination pills. Materials frame normalization and efficacy of combination medications and provide accurate information regarding common medication myths
5. **Nurse-directed Blood Pressure Clinics (Kaiser Bundle)** Providers can refer patients to a nurse-directed BP clinic within their clinic or at another clinic. Providers know how to refer patients, and there is a workflow for scheduling patients in those clinics	This EBP was adapted from pharmacist-directed to nurse-directed clinics to address a shortage of pharmacists and to incorporate existing nurse-directed clinics. We also added a CHW and Health Educator role to promote adherence	Some clinics have implemented nurse-directed BP clinics through pilot grants. There is variation in use among individual providers. The program is being scaled to other clinics	Provider webinars describe how to refer eligible patients to nurse-directed BP clinics	Patient educational materials inform patients about the nurse-directed BP clinic for supportive counseling on medications, dose adjustments, or concerns
6. **Culturally and Linguistically Tailored Education Materials** Patients with HTN receive culturally and linguistically tailored education materials at the end of the visit. These materials are available electronically for patients and providers	This EBP was adapted to include staff training on culturally responsive care and culturally and linguistically congruent outreach to patients	Culturally- and linguistically- tailored resources exist but have not been systematically circulated and organized. Care teams lack a straightforward way to access all relevant resources	Provider webinars describe the availability of culturally and linguistically tailored patient educational materials available on LAC DHS website, internal communication platforms, and printed in clinic. Provider webinars teach culturally responsive HTN care	Culturally and linguistically tailored educational materials may be sent to patients via text, patient portal, or hard copy in clinic/mail
7. **Screening for Social Needs and Linkage to Community Resources** Clinics systematically screen for social needs and refer patients to the Behavioral Health Integration Team for linkage to resources within their community	This EBP was adapted to include culturally relevant local resources for a variety of racial and ethnic groups	Social needs screening is embedded into standard primary care visit protocols, but there is varied awareness and understanding of the screening and referral processes. Once a patient screens positive and is referred to the Behavioral Health Integration Team, providers receive limited communication	Provider webinars educate providers on how to screen and refer patients to community resources	Patient educational materials discuss the value of community resources to meet social needs, including how to make self-referrals to some services
8. **Community Health Workers for Patients with HTN *****and***** Complex Medical and Social Needs** Clinics have a procedure in place to identify patients and refer them to the Behavioral Health Integration Team for linkage to CHWs	Not Applicable	CHWs are available system-wide to help address social needs and support engagement in medical treatment, but referrals to CHWs is inconsistent between providers and clinics. Variable integration of CHWs across different clinics results in their role being underutilized	Provider webinars educate providers on how to refer socially and medically complex patients to CHWs. Webinars for CHWs describe evidence-based and culturally relevant HTN care	Patient educational materials discuss the value of community resources to meet social needs
9. **Behavioral science to encourage behaviors related to HTN care** Behavioral science considers the environmental, social, and personal factors that impact how a person chooses to act	Not Applicable	Not Applicable	Clinics display posters to promote available resources and best practices for HTN care in provider charting and break rooms	Clinics display posters to promote best practices for HTN self-management in patient waiting areas and examination rooms. Messages sent to patients with uncontrolled HTN enhance patient engagement using behavioral science

*EBP* Evidence-based practice, *PCP* Primary Care Provider, *BP* Blood pressure, *HTN* Hypertension, *CHW* Community health worker, *LAC DHS* Los Angeles County Department of Health Services

The Kaiser Bundle includes a hypertension registry, standardization of blood pressure measurements, an evidence-based treatment protocol using fixed-dose combination medications, and medical assistant-led blood pressure clinics for medication adjustments. The Kaiser Bundle has been adapted and implemented in San Francisco safety-net clinics serving a racially and ethnically diverse patient population, where it improved blood pressure control across all racial and ethnic groups [20].

During the planning stage, we made several adaptations to the Kaiser Bundle. We incorporated home blood pressure monitoring (EBP #2); formulary additions to increase availability of combination medications (EBP #4); nurse-directed blood pressure clinics (EBP #5), culturally and linguistically tailored education materials (EBP #6); screening for unmet social needs like food insecurity, housing instability, and justice-involvement alongside linkage to corresponding health system and community resources (EBP #7); and CHW referral for medically and socially complex patients with high utilization or poor clinical outcomes (EBP #8). Our modifications were based on system-level barriers and potential facilitators identified by patients, providers, staff, and community members (e.g., culturally and linguistically tailored education, addressing social needs through community resources and CHWs); emerging evidence (e.g., home blood pressure monitoring recommended by new guidelines [12]); and practical considerations (e.g., availability of nurses for blood pressure clinics [60, 61], which LAC DHS was already introducing when we developed our project).

### Patient-focused strategies

Patient-focused strategies are designed to enhance patients’ access to culturally and linguistically tailored hypertension care resources and promote engagement in care.

#### Patient education materials

We developed patient educational materials based on American College of Cardiology/American Heart Association (ACC/AHA) guidelines, publicly available hypertension education resources, behavioral science, LAC DHS clinical guidelines, behavioral and cultural tailoring frameworks, and a rigorous iterative review process involving multiple partners. We incorporated insights from patient focus groups, CAB meetings, and healthcare personnel interviews conducted in the planning stage, which highlighted the value of addressing hypertension basics, common myths and misconceptions, medication adherence barriers, home blood pressure measurement techniques, and cultural and linguistic tailoring. We culturally tailored materials in consultation with patient focus groups, health system personnel, and ethnicity-specific CABs [42], and linguistically tailored materials using a translation vendor, followed by review by local native speakers. Four culturally concordant, multilingual graphic designers designed the finished products.

To date, we have developed 43 culturally and linguistically tailored patient education materials for five communities in English, Chinese (Simplified and Traditional), Korean, Spanish, and Tagalog. Education materials are designed to help patients understand hypertension, encourage home blood pressure measurement, promote blood pressure-lowering lifestyle habits, address medication-related concerns, increase awareness of clinic resources, and highlight health system resources for social needs (Table 3). To satisfy diverse learning needs, written materials were designed in several formats: comprehensive interactive handout packets, high-yield infographics, and informational posters for clinic waiting areas and exam rooms. Materials will be available on LAC DHS’s website. In the patient-focused strategy arm, patients will receive materials via patient portal, text message, or mail, per individual preference.

#### Videos

We also produced 2- or 3-min videos of patients describing lived experiences with hypertension. These can be played in clinic waiting rooms and placed on LAC DHS’s website.

#### Patient outreach

Patients with uncontrolled hypertension empaneled to clinics in the patient-focused strategy arm will receive messages through the patient portal or via text message. All messages contain a link to the culturally and linguistically tailored hypertension education materials described above. In addition, patients who have no primary care or nurse-directed hypertension clinic appointment scheduled within the next three months, or missed a primary care or nurse-directed hypertension clinic appointment within the last three months, will receive the following message: “Your care team needs to check your blood pressure and has saved an appointment for you. This visit is important to keep you healthy. Call *[clinic phone number]*to schedule your appointment within the next 3 months.” By stating, “Your care team has saved an appointment for you,” this message aims to increase clinic visits based on behavioral science insights that telling patients something is reserved for them enhances perceptions of selectivity and influences choice [62, 63]. We will send a follow-up message one week later, with up to three total messages per patient. For patients who do not complete a blood pressure management appointment after three messages, internal facilitators will conduct phone outreach to support scheduling.

### Provider-focused strategies

Care teams in clinics assigned to the provider-focused strategies will receive training to increase awareness about EBPs and provide guidance in their use (Table 3).

#### Provider webinars

We developed role-specific provider webinars for physicians, advanced practice providers, nurses, medical assistants, behavioral health providers, and CHWs. To design webinars, we collaborated with health system leaders with expertise in hypertension and health professions education. Webinars incorporated content from the ACC/AHA hypertension guidelines [12, 64] and LAC DHS expected practices. We tailored webinars using input from patients, ethnicity-specific CABs, and health system personnel, which underscored how social determinants, health literacy, and medical trust shape hypertension management. Informants also emphasized the value of culturally responsive care and recommended robust linkage to resources for unmet social needs [42]. Providers recommended clarifying nuances relating to evidence-based lifestyle recommendations, overlapping national guidelines, and therapeutic inertia. Patients recommended strategies to tackle adherence barriers, such as motivational interviewing, consideration of family context or social norms, and explanations of medications’ origins for those preferring holistic therapy.

To date, we have developed six webinars, including four 60-min sessions for physicians and advanced practice providers, one 60-min session for nurses, and one 60-min session for behavioral health staff and CHWs. These webinars are designed to educate providers on hypertension disparities within the health system, standardized guidelines for office-based blood pressure measurements, evidence-based lifestyle modifications, and fixed-dose combination medications on the LAC DHS formulary, along with delivery of evidence-based, culturally tailored hypertension care in their respective roles. Webinars also highlight clinic workflows, such as referrals for insurance-covered home blood pressure monitors, referrals to nurse-directed blood pressure clinics, and social needs screenings with linkages to CHWs, health educators, and community resources.

A peer champion will lead provider webinars over video conference within the first few months of provider-focused strategy initiation. Webinar completion is encouraged thorough endorsements by system leadership, email reminders, and continuing education credits where applicable. Following behavioral science insights on the motivational power of peer comparisons, we will recognize clinics for rates of webinar participation midway through the intervention year. Module recordings and slides will remain available through LAC DHS’s online training platform and commonly used communication platform.

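### Webinar recordings and patient materials are placed on shared health-system platforms with no stated arm limit, so usual-strategy clinics could reach passive content of both strategies in Year 1, the only control year

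*Protocol article*

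**What the plan says.** Under Provider webinars, the protocol article sets the timing: "A peer champion will lead provider webinars over video conference within the first few months of provider-focused strategy initiation". For Arm 3 that means early Year 1. It then says: "Module recordings and slides will remain available through LAC DHS’s online training platform and commonly used communication platform".

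Under Patient education materials it says: "Materials will be available on LAC DHS’s website". The next sentence ties active delivery to an arm: "In the patient-focused strategy arm, patients will receive materials via patient portal, text message, or mail, per individual preference". Of the patient videos it says: "These can be played in clinic waiting rooms and placed on LAC DHS’s website". In Table 3 (EBP 6, provider-focused column), the webinars tell providers about "patient educational materials available on LAC DHS website, internal communication platforms, and printed in clinic". The usual-strategy column of the same row describes the starting position: "Care teams lack a straightforward way to access all relevant resources".

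Under Study participants, every adult primary care clinic in the system takes part. The Overview of trial design gives Arm 1 usual strategies in Year 1 and both strategies in Year 2. The primary analysis compares Arm 1 with Arms 2 and 3 at the end of Year 1. In Table 5, item 8 gives one of nine points to any provider with at least one class attended, using course participation and CME requests.

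**The concern.** Every arm uses the same training platform, communication platform and website. Once Arm 3's recordings are posted, nothing in the article keeps an Arm 1 or Arm 2 provider from viewing them in Year 1. Once the patient materials are on the website, Arm 1 staff and patients can find them too.

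This content matters to the contrast. In Table 3, webinars are a provider-focused vehicle for EBPs 2 to 8, and patient educational materials are a patient-focused vehicle for the same rows. The usual-strategy condition for EBP 6 is partly defined by difficult access to resources, which open posting would ease.

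Two results depend on a clean Year 1 comparator: the primary implementation aim and Health-Related Aim 1. Any gain in Arm 1 from posted content shrinks the observed difference. Recordings would mainly weaken Arm 3 against Arm 1, and website materials mainly Arm 2 against Arm 1. Recordings viewed in Arm 2 act differently: they could raise Arm 2's score for reasons unrelated to the patient-focused strategy. The loss cannot be recovered later, because Arm 1 receives both strategies in Year 2.

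**Working it through.** **1. Which components carry an arm limit**

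| Component | Section | Arm limit stated? |
|---|---|---|
| Facilitation by assigned strategy | Implementation facilitation | Yes |
| Portal, text or mail delivery of materials | Patient education materials | Yes |
| Outreach messages, then phone calls | Patient outreach | Yes |
| Learning collaborative | Learning collaborative | Yes |
| Provider posters | Resource guide and provider-focused clinic poster | Yes |
| Webinar recordings and slides | Provider webinars | No |
| Patient materials on website and internal platforms | Patient education materials; Table 3 | No |

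The open route is therefore passive content. The recordings are placed in Year 1 by the webinar timing. The patient materials have no posting date. That Arm 3 webinars describe them as available suggests they are live in Year 1, but this is an inference.

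**2. The stated power** (Sample size and power considerations)

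Inputs: event rate 3, overdispersion 25%, ICC 0.05, repeated-visit correlation 0.3, 20 providers per clinic, 3% attrition, two-sided 5%. Nine sets of three clinics give 9 clinics per arm.

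- Variance = 3 × 1.25 = 3.75.
- Providers per clinic = 20 × 0.97 = 19.4.
- Design effect = 1 + 18.4 × 0.05 = 1.92.
- Variance of change with the correlation credited = 2 × (1 − 0.3) × 3.75 = 5.25.
- SE, 9 against 9 clinics = √(2 × 5.25 × 1.92 / (9 × 19.4)) = 0.340.
- Power = P(T₁₆ ≤ difference/SE − 2.12). At 1.46 this is 98% and at 1.24 it is 93%.

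With the variance taken under the alternative, power is 96% and 90%. If the 0.3 correlation is not credited, the variance of change is 7.5, the SE is 0.406, and power is 92% and 82%; with the variance under the alternative it is 89% and 78%. The stated figures (above 90% and above 80%) thus hold as lower bounds whenever the correlation is used. The power statement is not in error, but its listed assumptions make no allowance for control-arm exposure.

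**3. Illustration of dilution**

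Let c be the fraction of the active-arm effect that Arm 1 also gains. This is an assumption, as the documents give no figure. The observed difference becomes (1 − c) × d.

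Taking the stated power as exact (normal approximation), SE = 1.24/(1.96 + 0.842) = 0.443 and 1.46/(1.96 + 1.282) = 0.450. Then power = Φ((1 − c) × d/SE − 1.96).

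| c | d = 1.24 | d = 1.46 |
|---|---|---|
| 0 | 80% | 90% |
| 10% | 71% | 83% |
| 20% | 61% | 74% |
| 30% | 50% | 62% |

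For example, at c = 10% and d = 1.24: 1.116/0.443 − 1.96 = 0.56, and Φ(0.56) = 0.71. A t reference with 16 df gives 71% and 83% at c = 10%.

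Using SE = 0.340 from step 2 instead, c = 10% gives 1.116/0.340 − 2.12 = 1.16, or 87% power, and 1.314/0.340 − 2.12 = 1.75, or 95%. On that basis the loss is smaller.

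**4. Item 8 alone**

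Suppose 10%, 20% or 30% of Arm 1 providers score item 8 only because of recordings (an assumption). The difference then falls by 0.1, 0.2 or 0.3 points. With the stated power taken as exact and 16 df, 80% becomes 73%, 65% or 56%, and 90% becomes 86%, 80% or 73%.

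**The case against.** The strongest reply is that passive availability is not the strategy under test. Table 3 says tailored resources already exist under usual care but are poorly circulated; the trial tests active circulation, training and facilitation. A web page to which nobody directs Arm 1 patients does not make Arm 1 a patient-focused arm. This largely stands. A reader might infer that Arm 1 clinics could use both active strategies in full; the text does not support that, since the components marked as limited in the table above remain with assigned clinics.

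A second reply is that platform permissions and release dates may sit in the full protocol, which this article condenses. That is possible, and it is why the effect can only be called possible. But the article is not merely silent: it states arm limits for several components, and in consecutive sentences leaves website posting unlimited while limiting portal, text and mail delivery.

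Third, a reader might infer improper leakage of patient materials into Arm 3. Table 3 makes Arm 3 access to them partly deliberate, so that reading fails.

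Fourth, exposure is partly measured already. Item 8 covers all providers, the Outcomes section lists registration logs, and the Masking section lists webinar participation data. This stands in part: what is unsettled is whether a viewed recording counts.

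Finally, keeping patient education from control-clinic patients would sit badly with the equitable-access commitment given under Study development. That stands, and the fix below does not ask for it.

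**Conclusion.** The concern holds in limited form. As written, the plan leaves a route by which Arm 1 providers, and Arm 2 providers for the recordings, could reach passive core content of the active strategies in the only year with a usual-strategy comparator. Arm 1 uptake may bias the primary contrast and Health-Related Aim 1 toward no effect. It would cost power and understate the difference; it would not inflate type I error.

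The size is unknown. The 71% and 83% at 10% dilution rest on an assumed fraction and on reading the stated power as exact. A reader might take the larger losses in the tables as a forecast, but no exposure rate supports that, most components are out of Arm 1's reach, and the stated power figures are lower bounds. The clearest direct route is item 8, one of nine points, if a viewed recording counts as attendance. The change is worth making because it is cheap and the comparator cannot be restored after Year 1.

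**What to change.** - During Year 1, release webinar recordings and slides only to staff of clinics assigned to provider-focused strategies, by platform enrolment list. Open them to each other clinic when its arm reaches that strategy in Year 2.
- State whether a viewed recording counts for item 8, and apply the rule identically in all arms.
- Log module views and, where possible, material downloads by clinic. Report Arm 1 exposure in Year 1 beside the primary result.
- Leave patient materials on the website, without promoting them to Arm 1 clinics in Year 1.

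The cost is an enrolment list, access logging and a few protocol sentences. The downside is that Arm 1 and Arm 2 providers wait until Year 2 for the recordings, a delay the design already imposes on the provider-focused strategy itself. Some exposure through the website remains possible; logging would let it be described, not removed.
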